### Measurements

In the study, we will determine whether PRITAH is well implemented within these organizations. In parallel, the study will also measure the effect of the PRITAH-intervention by examining the types of involuntary treatment used in PLWD at home. Questionnaires will be collected at three points in time. A baseline measurement (T0) will be done after the kick-off meeting, but before the first PRITAH- workshop. T1 will be measured directly after the third PRITAH-workshop and T2 will be measured 12 weeks later (see Fig. 1). Both the control group and the intervention group will be measured at the same time intervals. In addition, data from observations from the PRITAH-training and evaluative focus group meetings will be collected during and after the PRITAH-training period.

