### PRITAH- intervention

The Prevention and Reduction of Involuntary Treatment At Home (PRITAH) intervention aims to support healthcare professionals and informal caregivers with knowledge and tools that can help prevent and reduce involuntary treatment at home. The intervention consists of four key elements: (1) implementation of policy in homecare organizations aimed to discourage the use of involuntary treatment; (2) a plenary kick-off meeting and three workshops for CMDs including practical assignments and case studies; (3) on-the-job coaching and consultation by a specially trained case manager in the field of dementia or common care nurse; and (4) availability and utilization of alternative interventions for involuntary treatment alternatives to prevent involuntary treatment use [28]. A summary of the four key elements is presented in Table 1.

**Table 1 Tab1:** Key elements of the PRITAH- intervention

Policy	The policy emphasizes that the organization will no longer apply involuntary treatment. It also sets clear conditions, such as raising awareness, adopting a multidisciplinary approach, maintaining communication with caregivers, and using alternatives. The policy is written and introduced to care professionals through the organization’s management.
***Education (2.5 h per workshop)***	Kick-off meeting - A general introduction to the PRITAH intervention and an overview of the three PRITAH- workshops by the research team. Workshop 1: increasing knowledge and awareness - Dilemmas about involuntary treatment, explaining the home care organization’s policy on its use, and providing an overview of current literature on its prevalence, risk factors, and consequences. Workshop 2: methodological approaches & alternatives - Methodological approach for situations involving involuntary treatment and exploring alternatives to prevent or reduce its use. Workshop 3: communication with stakeholders - Communication between caregivers, informal caregivers, and PLWD about involuntary treatment use, and using case studies to practice communication and for finding possible alternatives to involuntary treatment. Practical assignments between each workshop All workshops are given by specially trained nurses or case managers in the field of dementia care.

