#### Sample

The study will take place within the region of South Limburg in the Netherlands, home to a population of 402,700 individuals [38]. Of this population, 27.4% are 65 years or older and 2.2% (8,660 individuals) are diagnosed with dementia [39, 40]. In 2020, CMDs supported approximately 33–41% (i.e. 2,858 to 3,551) of the people living with dementia at home in the region [41]. In this large region, 88 CMDs employed by four professional homecare organizations are responsible for the dementia care in this region. Each CMD manages a caseload of approximately 55 clients (i.e. PLWD) in a fulltime position or proportionally in a part time position. All 88 CMDs working in the region of South Limburg in the Netherlands are invited to participate in the study on the implementation of the PRITAH-intervention. The CMDs are employed across four organizations in two regions and are each assigned to a specific city district or village within that region. To avoid contamination, all CMDs within the same district or village are grouped together, resulting in multiple clusters. These clusters are then allocated to either the intervention or the control condition, ensuring that CMDs within a given cluster did not interact across conditions. The CMDs in the intervention group receive training in batches of 10 to 14 people, with a two-week delay between the start of each batch’s training. CMDs in the control group will provide care as usual, continuing their routine work. They will not receive any PRITAH components (policy, kick-off meeting and training, on-the-job coaching and consultation, and alternatives for involuntary treatment). Moreover, CMDs in the control group are free to address involuntary treatment according to their usual practice in their respective organization. CMDs on maternity leave, long-term sick leave, nearing retirement, or newly recruited during the PRITAH-implementation period are excluded from the study. In a nested design, as part of the effect study, all 88 participating CMDs will report on the use of involuntary treatment by formal and informal caregivers for 10 randomly selected clients within their caseload to provide insights at the client level. If a client drops out of the study due to discontinuation of care (i.e. institutionalization or end of life), they will be replaced by another randomly assigned client from the caseload of the CMD. Therefore, we anticipate collecting 880 responses on client level. See Fig. 1.

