*Perceived behavioural control*	Sense of ease or difficulty in performing behaviours related to preventing involuntary treatment use			
*Intention*	Readiness or commitment to engage in behaviours related to preventing involuntary treatment use			
Discussions about involuntary treatment use	Whether the CMD discusses involuntary treatment use with the PLWD, formal caregivers (e.g., healthcare staff), and/or informal caregivers (e.g., family)	Questionnaire	CMD (IG & CG)	T0, T1, T2

T0 = 0 weeks (before PRITAH-workshop 1); T1 = 8 weeks after start PRITAH-workshop 1 (directly after finishing PRITAH-workshops); T2 = 20 weeks after start PRITAH-workshop 1 (12 weeks after finishing PRITAH-workshops)

IG = Intervention group; CG = Control group

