##### Effect outcomes

Outcomes at the CMD level (attitude, subjective norms, perceived behavioural control, and intention) will be analysed with mixed (multilevel) regression, with linear regression for continuous outcomes and generalized linear regression (e.g., logistic, ordinal, gamma) for categorical outcomes. A total score per CMD or client per time point will be calculated for each outcome measure if multiple items measure the same construct and share the same response format (e.g. all items are binary or all items use a 5-point Likert scale). Repeated outcome measures are nested within CMDs. The fixed (predictor) part of the mixed model will include intervention (yes/no), region, care organization, and time point (t0, t1, t2; week 0/8/20), along with age, gender, educational level, work experience in care for older people, work experience in professional home care, current position, number of working hours, and hours working with individuals with dementia. Additionally, interaction of each predictor with time will be evaluated. The random part of the model will account for unexplained outcome variation between CMDs, which is allowed to change over time, by assuming an unstructured residual covariance matrix (marginal model). Predictor by time interactions will be deleted if not significant, with exception of the key interaction between intervention and time. Giving the nonrandomized treatment assignment, additional analysis will be (a) comparing treated and controls with respect to the baseline outcome measurement, adjusted for all abovementioned confounders, and (b) repeating the above mixed regression, but now with the baseline outcome as covariate instead of as repeated measures. This approach will help assess Lord’s paradox as a sensitivity/robustness analysis [43, 55].

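### Baseline for the two-arm effect outcomes is taken after the kick-off meeting, a PRITAH component that only the intervention arm receives, so T0 is post-exposure in one arm

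*Protocol article*

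**What the plan says.** The Measurements section fixes the order of events: "A baseline measurement (T0) will be done after the kick-off meeting", and ahead of workshop 1. The note to Table 3 (Effect outcomes) gives only part of it, "T0 = 0 weeks (before PRITAH-workshop 1", and does not mention the kick-off.

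The section on the intervention puts the meeting inside the second of the four key elements, "a plenary kick-off meeting and three workshops for CMDs including practical assignments and case studies". Table 1 describes its content as "A general introduction to the PRITAH intervention and an overview of the three PRITAH- workshops by the research team". The Sample section says of the control group: "They will not receive any PRITAH components (policy, kick-off meeting and training, on-the-job coaching and consultation, and alternatives for involuntary treatment".

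Under Data analyses, Effect outcomes, T0 is used in three ways:
- It is one of the three repeated measures in the mixed model, where intervention by time is the key term and is always kept.
- It is the outcome of additional analysis (a), "comparing treated and controls with respect to the baseline outcome measurement, adjusted for all abovementioned confounders".
- It is the covariate in additional analysis (b).

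No measurement before the kick-off is described.

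**The concern.** A baseline should precede any part of the intervention in both arms. Here it does so only for controls. Measuring both arms at the same intervals aligns the calendar but not the exposure.

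This matters more than it would in a randomised trial. Allocation is not random, so the defence against confounding rests on a clean starting measurement, and analyses (a) and (b) were added for that reason. Both use the same T0, so neither can detect or repair a shift that has already occurred in one arm. All the effect outcomes are also reported by case managers who know whether they are being trained, so an early change in awareness or perceived expectation could show in their answers.

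**Working it through.** The article has no figure to reproduce. It makes no formal sample size calculation, and the point does not depend on alpha, power or a standard deviation.

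**Inputs from the article**
- The order of events and the control group's exposure, as quoted above.
- Feasibility-study changes (Background), used only as a scale: subjective norms 3.5 − 3.1 = 0.4; perceived behavioural control 3.9 − 3.6 = 0.3.

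**Assumed inputs**
- Share f of the full effect that arises at the kick-off: 10%, 25% or 50%.
- Slope b of follow-up on baseline: 0.5 or 0.7.

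**Algebra.** Let D be the full effect at follow-up, k the shift in the intervention arm caused by the kick-off before T0, and δ a pre-existing arm difference that is constant over time.
1. Intervention-by-time contrast: (δ + D) − (δ + k) = D − k.
2. Baseline as covariate: δ + D − b(δ + k), which is D − b·k when δ = 0.
3. T0 arm comparison: δ + k. The two parts cannot be separated.

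If T0 preceded the kick-off, k would be 0 in all three lines.

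**Illustration**, with k = f × D:

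| Scale (D) | f | Interaction D − k | Covariate, b = 0.5 | Covariate, b = 0.7 |
|---|---|---|---|---|
| Subjective norms (0.4) | 10% | 0.36 | 0.38 | 0.372 |
| | 25% | 0.30 | 0.35 | 0.33 |
| | 50% | 0.20 | 0.30 | 0.26 |
| Perceived control (0.3) | 10% | 0.27 | 0.285 | 0.279 |
| | 25% | 0.225 | 0.2625 | 0.2475 |
| | 50% | 0.15 | 0.225 | 0.195 |

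Worked line for subjective norms at 25%: k = 0.25 × 0.4 = 0.10. The interaction gives 0.40 − 0.10 = 0.30. The covariate model gives 0.40 − 0.5 × 0.10 = 0.35, or 0.40 − 0.7 × 0.10 = 0.33.

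**Reporting of involuntary treatment.** For simplicity this uses the prevalence scale rather than the planned total score. Assume true use of 50% in both arms and no effect. Let the kick-off raise reporting at T0 by a relative 5%, 10% or 20%, and let that rise fade by follow-up. The contrast then shows:
- 50 − 52.5 = −2.5 percentage points
- 50 − 55 = −5 percentage points
- 50 − 60 = −10 percentage points

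Each is an apparent reduction with no change in care. An early favourable shift works the other way and shrinks the estimate. The sign of the bias is therefore not fixed.

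**The case against.** The strongest reply is that the kick-off is slight. Table 1 describes an introduction and an outline of the workshops. The policy explanation, the evidence on prevalence and harm, and the alternatives come in workshops 1 and 2, after T0. Under Ethical considerations, all participants get a letter about the study's aims, so controls are not ignorant of the topic. This stands. A reader might infer that the baseline is demonstrably contaminated, or that only the intervention arm knows what the study is about. The documents support neither; they show a one-sided exposure, not a shift.

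The main effectiveness outcome is also the least exposed. It concerns what formal and informal caregivers do in clients' homes, and an introductory meeting for case managers has little obvious route to changing that before T0. This stands too, and leaves mainly a reporting route. A rise in reporting that persisted to follow-up would cancel out of the planned contrast; only a changing one distorts it.

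The illustrative figures are assumption applied to uncontrolled before-after changes in secondary outcomes. The article does not say whether the feasibility study's own T0 came before or after a kick-off. A reader might take 0.36 to 0.20 as an estimate of bias, but it only shows how the algebra behaves.

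Finally, the timing has a reason. Table 2 has intervention case managers rate adoption, acceptability and appropriateness at T0, and they need to have heard of PRITAH to do so. That justifies the timing for those items, which controls do not answer. It does not justify it for the outcomes compared between arms.

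**Conclusion.** The point holds on the article's own statements: T0 follows a component that one arm receives and the other does not, and no earlier measurement exists. As planned, the key interaction estimates the effect of PRITAH beyond the kick-off, not of PRITAH as defined. The covariate analysis recovers only part of any difference, and the T0 comparison cannot be read as pre-existing imbalance alone.

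Confidence is high for the sequence of events and low for the size of any bias. The value of k cannot be derived from the article, may be close to zero, and could have either sign. A reader might conclude that the effect will be underestimated. That follows only if the early shift is in the favourable direction, which is more plausible for the Theory of Planned Behaviour scales than for reported involuntary treatment.

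**What to change.** Split the baseline by purpose. Collect the effect questionnaire (involuntary treatment use and the Theory of Planned Behaviour scales) in both arms before the kick-off. Keep the adoption, acceptability and appropriateness items after it, in the intervention arm only. Amend the Measurements section and the notes to Tables 2 and 3 to match.

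The cost is small: two short baseline contacts instead of one in the intervention arm, with no extra measurement of the effect outcomes. If the kick-off is one plenary event for all groups, later groups will wait longer between T0 and workshop 1. With three training groups starting two weeks apart, the last starts (3 − 1) × 2 = 4 weeks after the first, so its T0 would fall at least four weeks before its workshop 1. Record actual dates and use actual time since T0 instead of the nominal weeks 0, 8 and 20.

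If T0 has already been collected after the kick-off:
- State that the estimate excludes any kick-off effect.
- Report the interval from kick-off to T0.
- Do not present the T0 arm comparison as purely pre-existing difference.

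Leaving out affected training groups is not a workable fallback, because the stated rule puts every group's T0 after the kick-off.

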#### Implementation outcomes

Primary outcomes for the PRITAH-implementation include adoption, acceptability, appropriateness, feasibility, fidelity, and sustainability, as defined by Proctor [45–47]. These outcomes are used to capture the initial uptake, practical integration, and long-term embedding of PRITAH within the healthcare organizations and CMDs [48]. The outcomes will be assessed using self-administered questionnaires based on Proctor’s definitions, PRITAH-training observations, PRITAH-training evaluation forms, attendance lists, and focus groups with PRITAH-trainers and managers of the organizations [46]. The questionnaires contain multiple statements for each outcome measure, with responses rated on a 5-point Likert scale ranging from totally disagree to totally agree. The development of the questionnaire is based on the Acceptability of Intervention Measure (AIM), Intervention Appropriateness Measure (IAM), and Feasibility of Intervention Measure (FIM) [45]. Furthermore, both the phrasing and the content of the statements were reviewed by experienced researchers in implementation science to assure face validity. To complement data on the implementation outcomes, additional qualitative data will be collected. During the nine PRITAH-workshop sessions (three training groups with three sessions each), a member of the research team takes observations through field notes to assess whether the trainers adhered to the protocol and whether modifications were made. PRITAH-training evaluation forms, containing both closed and open-ended questions are distributed and completed after each workshop to gather feedback on that specific session. The output of these evaluation forms will be used as input for the two focus group meetings with both PRITAH-trainers and managers from the participating organizations. Lastly, attendance lists are recorded. See Table 2 for a summary of the implementation outcomes and measurements.

**Table 2 Tab2:** Implementation outcomes

Implementation outcome (Proctor, 2011)	Operationalisation description	Measurement	Target group	Timepoint
Adoption	The intention and decision to engage with PRITAH and its four key elements, reflecting how well the intervention is embraced by healthcare professionals	Questionnaire PRITAH-training evaluation forms Focus group meeting	CMD (IG) Trainers Managers	T0, T1
Acceptability	The perception among CMDs that PRITAH is agreeable, acceptable, and satisfactory, measuring how well the intervention is received and appreciated by those who are expected to implement it	Questionnaire PRITAH-training evaluation forms	CMD (IG)	T0, T1
Appropriateness	The perceived fit, relevance, and compatibility of the PRITAH- intervention within the homecare setting and within the needs of CMDs and PLWD, evaluating whether the intervention is seen as suitable for the context (i.e. professional homecare organizations) in which it is being applied	Questionnaire	CMD (IG)	T0, T1
Feasibility	The practicality of implementing PRITAH within the organization, evaluating its fit and functionality in the professional homecare settings	Questionnaire PRITAH-training evaluation forms Focus group meeting	CMD (IG) Trainers Managers	T1, T2
Fidelity	The degree to which PRITAH-intervention is delivered as intended, ensuring that the intervention is implemented accurately and consistently according to the designed protocol and guidelines	Observations (field notes) Attendance lists	Members from the research team Trainers	T1
Sustainability	How well the PRITAH- intervention is integrated into the organization’s routine processes and embedded into its culture through established policies and continuous practices	Questionnaire	CMD (IG)	T2

*T0* = 0 weeks (before PRITAH-workshop 1), *T1* = 8 weeks after start PRITAH-workshop 1 (directly after finishing PRITAH-workshops), *T2* = 20 weeks after start PRITAH-workshop 1 (12 weeks after finishing PRITAH-workshops

*IG* Intervention Group

#### Effect outcomes

The primary outcome of the PRITAH- effectiveness is the use of involuntary treatment in PLWD at home, including non-consensual care, physical restraints, and psychotropic medication (i.e. off-label use). Involuntary treatment use will be measured at baseline (T0), T1, and T2 using questionnaires spread under CMD’s. The questionnaire is based on the questionnaire that was developed by Hamers et al., which was also used to assess the prevalence of involuntary treatment by Moermans et al. [17, 19]. It comprises 25 types of involuntary treatment categorized into the two forms (12 types of physical restraint, 13 types of non-consensual care), and includes two separate questions about the use of psychotropic medication. CMDs will use the self-administered questionnaire to indicate whether each type of involuntary treatment is used for ten randomly assigned PLWD within their caseload. Secondary outcome measures involve mechanisms of impact assessed through a self-administered questionnaire based on the Theory of Planned Behaviour, which was used by Mengelers in the pilot/feasibility study for PRITAH-intervention [31, 49]. CMDs’ attitudes (20 items), subjective norms (5 items), perceived behavioural control (9 items), and intention (4 items) will be rated on a 5-point scale ranging from 0 (totally disagree) to 5 (totally agree). Four additional items are included to gather information about the CMDs characteristics, including age, educational background, work experience, and workload perception. Lastly, three additional questions address whether the CMD discusses involuntary treatment use with the person with dementia, and/or their formal and informal caregivers. See Table 3 for an overview.

**Table 3 Tab3:** Effect outcomes

Effect outcomes	Description	Measurement	Target group	Timepoint
Involuntary treatment use in PLWD at home	The extent to which involuntary treatments (i.e. non-consensual care, physical restraints, and psychotropic medication) are used in PLWD at home	Questionnaire	CMD (IG & CG)	T0, T1, T2
Mechanisms of impact:	Mechanisms of impact regarding involuntary treatment use based on the Theory of Planned Behaviour (49)	Questionnaire	CMD (IG & CG)	T0, T1, T2
*Attitude*	Settled way of thinking or feeling about involuntary treatment use			
*Subjective norms*	Perception of social pressure from significant others regarding involuntary treatment use			
*Perceived behavioural control*	Sense of ease or difficulty in performing behaviours related to preventing involuntary treatment use			
*Intention*	Readiness or commitment to engage in behaviours related to preventing involuntary treatment use			
Discussions about involuntary treatment use	Whether the CMD discusses involuntary treatment use with the PLWD, formal caregivers (e.g., healthcare staff), and/or informal caregivers (e.g., family)	Questionnaire	CMD (IG & CG)	T0, T1, T2

T0 = 0 weeks (before PRITAH-workshop 1); T1 = 8 weeks after start PRITAH-workshop 1 (directly after finishing PRITAH-workshops); T2 = 20 weeks after start PRITAH-workshop 1 (12 weeks after finishing PRITAH-workshops)

IG = Intervention group; CG = Control group

### Data analyses

Depending on the distribution of the data means with standard deviations or medians with interquartile range will be presented for interval and ratio variables. For ordinal and nominal variables frequencies and percentages will be reported. Data will be analysed using SPSS statistics version 28. Cases will be excluded for whom no data have been collected at any of the three timepoints. Qualitative data will be analysed by using qualitative analysis software MAXQDA 24.

